## Methods: participants, interventions, and outcomes

### Study setting {9}

eliPfad will be conducted as a multicenter trial in 5 centers with 6 corresponding hospitals and the home environment of each patient. The participating centers/hospitals are the University Hospital Cologne, University Hospital Aachen, Hospital Dortmund, Hospital Herne, and as one center with two corresponding hospitals the St. Franziskus Stiftung in Münster with St. Franziskus Hospital and Hospital Hiltrup. So far, two physician networks in Cologne and Münster participate in eliPfad and represent the ambulatory sector. Patients are enrolled into the new model of care eliPfad during a hospital stay (index hospital stay) which continues after discharge in the home environment. After discharge, patients will be visited at home by the “case manager” (introduced later).

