### Eligibility criteria {10}

The inclusion criteria are:Emergency hospital admission or transfer to a normal internal medicine ward in the form of:Direct admission from home / the referring GPAdmission from the emergency departmentTransfer from another hospital (reason for admission: internal medicine)Transfer from another ward within the hospital with initial admission due to an internal diseaseAge ≥55 yearsMultimorbidity (presence of at least 3 long-term health conditions)At least one of the following index diagnoses:Heart failure (NYHA I-IV)Chronic kidney disease (CKD)Chronic obstructive pulmonary disease (COPD)Diabetes mellitus (DM)Peripheral artery disease (PAD)Coronary heart disease (CHD)Arterial hypertension (AH)High risk of unplanned readmission (risk assessment by Multidimensional Prognostic Index (MPI) ≥0.34)Written informed consent, documented by signature, after sufficient reflection period. Patient-informed consent cannot be obtained during a medical emergency

The exclusion criteria are:Patients admitted to the hospital due to a non-internal disease (this includes the reason for initial admission to the referring hospital)Patients likely to be released from hospital within 2 working daysResidents of nursing facilities, home-based 24-h care, predominantly bedridden patientsLack of rehabilitation potential according to the attending physician’s assessmentInsufficient command of German language among patients and relatives/friendsA higher degree of visual and/or hearing impairment, if no relatives availableDiseases with a life expectancy of less than 6 monthsDesired rehabilitation on days 1 to 42 after discharge from index hospitalizationTravel distance from participating hospital to patient’s home 50 km or more (exceptions based on individual decision are possible) Patients with full private health insurance Patients who are in a dependent/employed relationship with the investigators Lack of capacity to consent Placement in an institution by court or official order

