## Assignment of interventions: allocation

### Sequence generation {16a}

Sequence generation is performed by the electronic data capture system (EDC, secuTrial®), which also provides the electronic case report form (eCRF). The software’s own “Extended Stratified Block without List” is used here, which represents a stratified block randomization. Factors for stratification are center and sex. Because of the 6 centers, there will therefore be 12 strata.

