## Statistical methods

### Statistical methods for primary and secondary outcomes {20a}

The primary analysis set is derived according to the intention-to-treat-principle (treatment policy strategy): All patients who are included in the study and randomized are analyzed in their allocated group. A secondary analysis set is defined according to the hypothetical strategy (per protocol), comprising all included, eligible, and randomized patients who proceed without interruptions (especially transfers) from stationary to ambulant care. The primary null hypothesis is tested using negative-binomial regression of the number of individual readmissions on the group, if it converges to a solution on the collected data, assuming overdispersed data. In case of equidispersion or non-convergence of the negative-binomial regression, Poisson regression is used. Models will include age, sex, study site, offset (log time under risk), and robust variance-covariance estimation (clustered sandwich estimator) (Stata/SE 17.0, StataCorp LLC, College Station, TX, USA; call: poisson/nbreg outcome group, sex age study.site offset(log.time.under.risk) irr vce(cluster patient.id)). Negative-binomial regression is favored if it converges to a solution on the collected data. Other possible confounder will be specified in the SAP after discussion by clinicians and evaluators and variables will be included in the analysis. Time under risk is defined as the time patients spend at home or in a care facility that does not have medical staff on duty. If a patient dies, they will no longer contribute time under risk from this point onwards. In case of underdispersed data a generalized Poisson model is considered, which is capable of dealing with underdispersion. For the main effect group (relative rate reduction), the *p*-value and the associated two-sided 95% confidence interval are determined. The significance level is 5% two-sided.

The regression approach can take into account the shorter time under risk (than 6 months), especially due to loss-to-follow-up or dropout. The main estimator here is the ratio of event rates (defined as the total number of readmissions/sum of risk times) of intervention to the control group.

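### The primary model does not name baseline MPI, the trial's own readmission-risk score, and the printed model call and the number of site levels need correcting (low severity)

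*Protocol article*

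**What the plan says.** Under Statistical methods {20a} the primary test is a negative-binomial or Poisson regression of the number of readmissions on group. The covariates are fixed in prose: "Models will include age, sex, study site, offset (log time under risk), and robust variance-covariance estimation (clustered sandwich estimator". A Stata call is printed beside it: "poisson/nbreg outcome group, sex age study.site offset(log.time.under.risk) irr vce(cluster patient.id". The same paragraph leaves the list open: "Other possible confounder will be specified in the SAP after discussion by clinicians and evaluators and variables will be included in the analysis".

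Under Eligibility criteria {10}, one inclusion criterion reads "High risk of unplanned readmission (risk assessment by Multidimensional Prognostic Index (MPI) ≥0.34". Recruitment {15} has the case manager assess MPI when checking eligibility, and Table 1 places that assessment at enrolment.

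Randomisation is stratified by center and sex. Sequence generation {16a} says "Because of the 6 centers, there will therefore be 12 strata". Study setting {9} describes a "multicenter trial in 5 centers with 6 corresponding hospitals", and the oversight section {5d} repeats that the two Münster hospitals form one center.

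**The concern.** Three things in the specification of the primary model do not sit well together.

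1. The trial selects patients on a score because it marks risk of unplanned readmission, and the primary outcome counts unplanned readmissions. Yet the score is not among the named covariates. Further terms are to be chosen as confounders. Randomisation already deals with confounding; a baseline covariate earns its place by predicting the outcome. A choice made later under the wrong criterion could leave out a useful predictor.

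2. The printed call does not do what the prose says.

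3. The number of levels of the site factor is uncertain, and it should match the factor used for stratification.

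At stake is some precision in the primary comparison, and a clear record of what was prespecified in an open-label trial. Validity of the estimate is not at stake.

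**Working it through.** **Step 1: the plan's own figure.** Inputs from Sample size {14}: control p = (0.35, 0.40, 0.20, 0.05), intervention q = (0.495, 0.331, 0.149, 0.025), t = 0.5, 90% power, two-sided 5%. The ordered-category Wilcoxon formula is N = (1.960 + 1.282)² × [1 − Σ((p+q)/2)³] / {12 × 0.25 × A²}, where A is the probability that a control count exceeds an intervention count, plus half the probability of a tie, minus 0.5.

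- A = 0.41195 + 0.16835 − 0.5 = 0.0803
- 1 − Σ((p+q)/2)³ = 0.8704
- N = 10.507 × 0.8704 / (3 × 0.0803²) = 472.8, which rounds up to the stated 474 when made even
- Dropout: 237/(1 − 0.5) = 474 per arm, 948 in total, as stated
- Means 0.95 and 0.704 give a rate ratio of 0.741, a 25.9% reduction, as stated

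Power of a robust Poisson test under these distributions is 0.88 (formula) to 0.89 (simulation) at 237 v 237, and 0.93 at 237 v 332 (332 ≈ 0.7 × 474). This is consistent with the stated 90%. The variance-to-mean ratios are 0.79 and 0.93, so the planning scenario holds no extra-Poisson variation for a covariate to explain.

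**Step 2: gain from MPI (assumed range).** No document gives a slope, so let the log rate rise by b per SD of MPI, and let κ be the remaining overdispersion. With means m₀ = 0.95 and m₁ = 0.704:

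- Adjusted: Var = (1/m₀ + κ)/n₀ + (1/m₁ + κ)/n₁
- Unadjusted: the same with κ replaced by (1 + κ)·exp(b²) − 1
- Power = Φ(|ln 0.741|/SE − 1.96)

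Example for b = 0.4, κ = 0, 237 per group. Adjusted variance = (1.0526 + 1.4205)/237 = 0.01043. Unadjusted variance = (2.4731 + 2 × 0.1735)/237 = 0.01190. Saving = 1 − 0.01043/0.01190 = 12.3%. Power goes from 78.4% to 83.5%.

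| Rate ratio per SD of MPI | Saving in N (κ = 0 / 0.5 / 1.0) | Power, κ = 0 | Power, κ = 0.5 |
|---|---|---|---|
| 1.11 | 0.8 / 0.9 / 0.9% | 83.2 → 83.5% | 69.3 → 69.7% |
| 1.22 | 3.2 / 3.4 / 3.5% | 82.3 → 83.5% | 68.2 → 69.7% |
| 1.35 | 7.1 / 7.5 / 7.8% | 80.7 → 83.5% | 66.3 → 69.7% |
| 1.49 | 12.3 / 13.0 / 13.4% | 78.4 → 83.5% | 63.6 → 69.7% |

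Only the differences matter here. The absolute powers rest on added variation that the plan does not assume. The formula also gives no credit for age, which is already in the model.

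**Step 3: the call.** In Stata, options follow the comma. As printed, sex, age and site stand in the option position, so the line fails; the dotted variable names and the slash between two commands would stop it as well. With the comma moved, site without an i. prefix is a single linear term.

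**Step 4: cost of linear site.** This was simulated with center-stratified blocks, robust Poisson and 2,000 trials per scenario; the site SDs on the log-rate scale are assumed.

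| Site SD, b, κ | Coding | Empirical SD | Mean SE | Power |
|---|---|---|---|---|
| 0.2, 0.2, 0.5 | linear | 0.1213 | 0.1245 | 0.683 |
| 0.2, 0.2, 0.5 | factor | 0.1212 | 0.1231 | 0.695 |
| 0.3, 0.4, 0.5 | linear | 0.1325 | 0.1327 | 0.625 |
| 0.3, 0.4, 0.5 | factor | 0.1325 | 0.1303 | 0.635 |

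The estimate is equally variable either way, because stratification balances the sites. Only the reported SE falls, by 1% to 2%. Under no effect (site SD 0.3, b = 0.3, κ = 0.5) the type I error was 0.052 with linear site, 0.059 with factor site and 0.065 with factor site plus MPI. The last is high for 2,000 trials, so that scenario was repeated with 8,000 trials at 237 per group; it gave 0.048, 0.052 and 0.053.

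**Step 5: centers.** 5 centers × 2 sexes = 10 strata; 6 × 2 = 12. The stated 12 fits six hospitals, not the five centers listed elsewhere.

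**The case against.** The strongest reply is that the covariate list is open. The article says that more variables will come with the SAP, which is not shown, so MPI may well be named there. That stands. A reader might infer that the plan excludes MPI, or leaves out its strongest predictor; the documents support neither. They give no MPI–readmission association. The Background names other predictors (higher age, multimorbidity, heart failure, coronary heart disease, chronic kidney disease, COPD), and age is already in the model. The entry cut at 0.34 also narrows the spread of MPI among trial patients. What does not fall away is the criterion: choosing later terms as confounders is the wrong test in a randomised trial.

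A second reply is that the call is only a sketch. That also largely stands. The prose says just that study site is included, site is a stratification factor, and no section calls it continuous. A reader might infer that site will be fitted as a linear number and that real power will be lost; a line that cannot run is weak evidence for the first, and Step 4 shows almost nothing for the second. It is still the one explicit specification of the primary test and should be right.

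A third reply is that the center count is explained by one center having two hospitals. This explains five against six, but not why the randomisation section calls all six centers.

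**Conclusion.** The point holds as a low-severity improvement to the specification. MPI is not named for the primary model although it is the trial's own risk score and is available before randomisation in every eligible patient. Naming it is worth about 1% to 13% of N, or under 0.5 to about 6 power points, if the rate ratio per SD of MPI lies between 1.11 and 1.49. That range is assumed, and the truncation at 0.34 makes its lower part more likely. The printed call is wrong as it stands. Reading site as linear would cost between nil and about 1 power point at assumed site SDs of 0.2 to 0.3. Neither matter biases the rate ratio or inflates type I error, and the sample sizes of 474 evaluable and 948 randomised are unaffected. The 5 v 6 center discrepancy is a genuine inconsistency that leaves the number of site levels undefined.

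**What to change.** - Prespecify MPI as a continuous covariate in the primary model, alongside age, sex and site. Define it as the screening value, because A0 takes place after randomisation in an open-label trial.
- State that any further covariates are chosen for prognostic value, and close the list in the SAP before outcome data are seen by group.
- Enter site as a categorical factor with exactly the levels configured in the randomisation system.
- Correct the call, for example: `nbreg outcome i.group age i.sex i.site mpi, offset(logtime) irr vce(cluster id)`, and the same line with `poisson`.
- Reconcile five centers with six centers and 12 strata across Study setting {9}, Sequence generation {16a} and the oversight section {5d}.

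The cost is a few sentences in the protocol and SAP. No new data, visits or patients are needed, because MPI is already collected to establish eligibility.

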#### Time frame of the intervention

Patients are enrolled within two working days after admission to an internal ward (see eligibility criteria above) and the hospital part of eliPfad begins. After discharge from the index hospital stay, patients will be treated in eliPfad for 42 days in the ambulatory setting. This time frame is fixed and will not be prolonged due to planned or unplanned hospital stays within the 42 days. Should the patient be admitted to a hospital within 42 days, the intervention would pause during that period and resume afterward—given that the 42nd day after the initial discharge is not yet reached. A follow-up visit is planned 6 months after the discharge from the index hospital stay.

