### Sample size {14}

Based on literature data and own calculations using data from the collaborating health insurance companies, a relative reduction of the readmission rate of about 25.9% over 6 months after (initial) discharge is expected (see also Berntsen et al, admission rate of 1.89/year corresponding to 0.95 over 6 months) (19) with the following distribution of absolute numbers (#) of readmissions per patient: #0—35%, #1—40%, #2—20%, #3—5% (Ø 0.95). eliPfad will result in a compression of this distribution as listed below: #0—49.5%, #1—33.1%, #2—14.9%, #3—2.5% (Ø 0.704). The Wilcoxon rank sum test was used to calculate the number of cases; by stratification, a power gain is additionally expected. Accordingly, a total of 474 patients (237 per group) are needed to detect this distribution difference with a power of 90% with a two-sided type I error of 5% [40] (R: A Language and Environment for Statistical Computing, Vienna, Austria, package samplesize, call: n.wilcox.ord (power = 0.9, alpha = 0.05, *t* = 0.5, *p* = c(0.35, 0.40, 0.20, 0.05), *q* = c(0.495, 0.331, 0.149, 0.025))). To compensate for up to 50% loss-to-follow-up in the control group and 30% in the intervention group, 474 patients should be randomized to each of the two groups (total 948 = 474/0.5). In the scenario given above, for the evaluation of the primary outcome measure using Poisson regression, the power of at least 90% was confirmed by simulation.

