Secondary analyses models will also include strata and confounder. The frequencies of repeated events like number of rehabilitation services or transfers to acute geriatric units between T1 and T3 (health insurance companies’ data) and time variables like duration of stay in index hospital, intensive care unit, external hospitals, or rehabilitation facilities will be analyzed analogous to the primary endpoint. Patient questionnaire scales will be evaluated by linear mixed models with repeated measurement over time. Time to death will be analyzed by Cox regression.

In general, quantitative target variables are described by the number of valid cases, mean ± standard deviation, and percentiles (0, 25, 50, 75, 100), and qualitative target variables by absolute and relative (%) frequencies, over time.

All details and methods of statistical analysis will be documented in a statistical analysis plan (SAP). The SAP shall be finalized before database closure and will be approved by the two principal investigators and representatives of the evaluating statistics departments.

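### Index-stay and intensive-care durations are compared between arms over the whole index stay, so in-house days before randomisation dilute any true ratio; a minor, cheaply corrected point on secondary outcomes

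*Protocol article*

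**What the plan says.** All references are to the protocol article.

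- **What is compared.** Statistical methods for primary and secondary outcomes {20a} lists "time variables like duration of stay in index hospital, intensive care unit, external hospitals, or rehabilitation facilities" among the variables to be analysed like the primary endpoint. That means negative-binomial or Poisson regression, with a ratio between arms as the estimate.
- **What is recorded.** Outcomes {12} lists the duration of the index hospital stay, and the time in intensive or intermediate care units within that stay. Neither item is said to start at randomisation.
- **What the index stay is.** Study setting {9}: "Patients are enrolled into the new model of care eliPfad during a hospital stay (index hospital stay". It is the stay in which enrolment happens; it does not begin with enrolment.
- **When patients are randomised.** Time frame of the intervention: "Patients are enrolled within two working days after admission to an internal ward". Outcomes {12} puts the baseline assessment directly after randomisation and on the same ward-admission clock.
- **Who may enter.** Eligibility criteria {10} requires a normal internal medicine ward. It accepts patients moved from another ward of the same hospital if the initial admission was for an internal disease. It sets no limit on the days already spent there and does not exclude intensive care as the earlier ward.

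**The concern.** A treatment comparison should count what can happen after allocation. Read as written, these two durations also include in-house days that were over before the patient was randomised. Randomisation makes those days equal in expectation in the two arms, so they add the same amount to the numerator and the denominator of the ratio and pull it toward 1. Their spread adds noise as well.

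If eliPfad does shorten the hospital phase, the reported ratio would understate this. A ratio near 1 could not be separated into no effect and dilution. Intensive-care days are the more exposed of the two outcomes: a patient must be on a normal ward to be randomised, so an intensive-care spell before arrival there lies wholly before allocation.

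**Working it through.** **The plan's own figure.** The document gives a calculation for the primary outcome only: "a total of 474 patients (237 per group) are needed to detect this distribution difference with a power of 90"%. With the two stated readmission distributions, the ordinal Wilcoxon formula N = (z₀.₉₇₅ + z₀.₉₀)² × (1 − Σ pooled p³) / (12·t(1−t)·(P − 0.5)²), with t = 0.5 and P = 0.5803, gives N = 472.8, which is 474 with equal groups. Then 237/0.5 = 474 randomised per group. The figure reproduces. It has no bearing on the durations, for which the document gives no mean, spread or expected effect.

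**Dilution formula.** Let a be the mean days before randomisation (equal in both arms), m the mean days after it in the control arm, and R the true ratio of post-randomisation days. The whole-stay ratio is (a + R·m)/(a + m) = s + (1−s)R, with s = a/(a + m). For any s > 0 it lies between R and 1. If R = 1 it stays at 1.

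**Index stay, assumed inputs.** m = 8 days, SD 6 (scaled with the mean in the intervention arm), R = 0.85, 474 per arm, all contributing, and prior days uncorrelated with later days. Power is a normal approximation on the log ratio of means, SE = √(CV₀²/474 + CV₁²/474), two-sided 5%.

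- Counted from randomisation: CV = 0.75 in both arms, SE = 0.0487, z = 0.1625/0.0487 = 3.34, power about 92%.
- One mean prior day: (1 + 6.8)/9 = 0.867. Two: (2 + 6.8)/10 = 0.880. Three: (3 + 6.8)/11 = 0.891.

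| Prior days, mean (SD) | Ratio shown | Power |
|---|---|---|
| none counted | 0.850 | 92% |
| 1 (1) | 0.867 | 91% |
| 2 (1) | 0.880 | 91% |
| 3 (1) | 0.891 | 91% |
| 1.5 (1.5) | 0.874 | 90% |
| 3 (4) | 0.891 | 77% |

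The estimate shrinks in every row with prior days. Power drops materially only when prior days vary a lot. With SD 1 the coefficient of variation falls almost in step with the log ratio, so little power is lost.

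**Simulation.** There were 4,000 runs with 474 per arm, a gamma stay after randomisation (mean 8 days), prior days of 0 to 2 for all patients, and longer prior stays for some.

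- R = 1: rejection stayed at about 5% with whole-stay counting.
- R = 0.90: power was about 63–65% when counted from randomisation. With whole-stay counting it was 64%, 50% and 33% at mean prior days of 1.0, 1.9 and 3.4.

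**Intensive-care days, assumed inputs.** Four days per episode, R = 0.80, a proportion f arriving via intensive care and a proportion g needing it after randomisation, so s = f/(f + g).

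- f = 0: s = 0, ratio 0.80, no dilution.
- f = 5%, g = 10%: s = 0.33, ratio 0.33 + 0.67 × 0.80 = 0.867.
- f = 30%, g = 3%: s = 0.91, ratio 0.982.

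The document gives neither f nor g, so the answer runs from no dilution to almost complete dilution.

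**The case against.** The strongest reply is that the start of a duration count is SAP detail. The article gives short variable names, leaves the details of analysis to an SAP that is not shown, and says the secondary models will include strata and confounders. This stands in part: the SAP may start the count at randomisation. But the article does state a window for intensive care, namely the index stay, while its insurance-data items run between T1 and T3. An SAP that followed the article would count days before randomisation.

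Second, the secondary hypotheses in section 7 name neither index-stay length nor intensive-care days, and no expected effect on them is stated. Whole-stay length is also a legitimate descriptive quantity, and an absolute difference in days is not diluted. All of this stands and holds the severity down.

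Some stronger readings are tempting, but the document does not support them:

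- **That every patient's total contains prior days.** Enrolment within two working days allows the same day, and a direct admission without earlier intensive care has no prior intensive-care days.
- **That prior days swamp the intensive-care outcome, or make it mainly a record of baseline history.** That needs the share arriving from intensive care, which is not given.
- **That days at a referring hospital inflate the index stay.** External-hospital stays are listed separately, and nothing shown adds the referring hospital's days to the index total.
- **That power collapses.** Prior days of mean 5 and SD 8 would bring power to 47%, but that needs many long earlier stays, for which the document gives no basis.

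**Conclusion.** The point holds as a minor one. Followed as written, the plan counts in-house days before randomisation in two between-arm comparisons, and any non-null ratio is then pulled toward 1. For patients admitted directly to the ward, the window is at most two working days and the effect is modest: under the assumed 8-day stay, a true 0.85 appears as about 0.87 to 0.88 with one to two prior days, and power hardly changes. The loss grows only if in-house transfers bring long and variable earlier stays; 77% power with mean 3 and SD 4 illustrates this under assumed values. For intensive-care days the size cannot be determined from the document.

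The error is attenuation with some lost precision, not false positives. The primary outcome is counted after discharge and is untouched. All sizes rest on assumed stays, spreads and effects, and on the plain reading of the recorded variables as whole-stay totals.

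**What to change.** In Outcomes {12} and Statistical methods {20a}, or in the SAP before database closure:

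1. Define the compared outcomes as days from randomisation to discharge from the index stay, and intensive/intermediate-care days after randomisation.
2. Enter the in-house days before randomisation (total, and intensive/intermediate care) as a baseline covariate in the respective models.
3. Report whole-stay totals by arm descriptively only.

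The cost is wording and some extra derivation. Randomisation runs in the electronic data capture system, so its date should be available, and admission and ward dates are presumably needed for the durations already recorded. No patients or visits are added. The small downside is that days from randomisation is a less familiar measure than length of stay; the descriptive whole-stay table covers that.
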